## Abstract

**Background:**

Theory of Mind (ToM) refers to the ability to represent one's own and others' mental states, and emotion understanding involves appropriately comprehending and responding to others' emotional cues in social interactions. Individual differences in mind and emotion understanding have been associated strongly with verbal ability and interaction and, as such, existing training for children's ToM and emotion understanding is mostly language-based. Building on the literature on embodied cognition, this study proposes that mind and emotion understanding could be facilitated by one's visuospatial experience in simulating other's frames of reference.

**Methods:**

This protocol consists of two training studies. Study 1 will examine if visuospatial perspective-taking training promotes ToM and emotion understanding. Participants will consist of 96 4.5-year-olds and will be randomly assigned to one of two training groups: the altercentric block building group (trained to be visuospatial perspective-takers), or the egocentric block building group (no visuospatial perspective-taking is involved). Study 2 will compare the engagement of visuospatial perspective-taking and verbal interaction in the development of mind and emotion understanding. Participants will consist of 120 4.5-year-olds. They will be randomly assigned to one of three training groups: the socialized altercentric block building (both visuospatial perspective-taking and verbal interaction), the parallel altercentric block building (visuospatial perspective-taking only), or the paired dialogic reading (verbal interaction only).

**Conclusions:**

In terms of theoretical implications, the potential causal relationship between visuospatial perspective-taking and ToM and emotion understanding may shed new insights on what underlies the development of mental state understanding. The findings of this study also have practical implications: researchers and educators may popularize visuospatial perspective-taking training in the form of block-building games if it is found to be effective in complementing conventional language-based theory-of-mind training.

## Background

Theory of Mind (ToM) is the ability to ascribe mental states, such as desires, intentions, beliefs, or feelings, to oneself and others in social interactions [1]. Children recognize that the mental states of others may differ from their own when they acquire ToM. As such, children with ToM interact with others based on their interpretation of mental states of the other people. ToM and emotion understanding are related to one another and are conceptually interrelated [2, 3]. Emotion understanding involves comprehending and responding to emotional cues appropriately in social interactions [4]. Children's early social relationships are essential to developing ToM and emotion understanding [5], and children exposed to a conversation-rich environment have improved ToM and emotion understanding [6–8]. Ontogenetic studies show that the acquisition of ToM emerges between the ages of 3 and 5 [9, 10], but individual differences in ToM development often occur, and these individual differences in ToM are strongly associated with verbal ability and interaction [5, 11, 12].

Building on the literature on embodied cognition and visuospatial perspective-taking, this study proposes that mind and emotion understanding could be facilitated by one's visuospatial experience in simulating the frames of reference of others. This proposal consists of two visuospatial perspective-taking training studies:Study 1 aims to demonstrate that visuospatial perspective-taking training promotes ToM and emotion understanding development in preschoolers.Study 2 aims to reproduce the results of Study 1, and more importantly, to elucidate and compare the engagement of visuospatial perspective-taking and verbal interaction in the development of mental state understanding.

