### The present study

This proposal draws on the literature of embodied cognition and visuospatial perspective-taking to explore alternative approaches to promote early mind and emotion understanding. The potential role of visuospatial perspective-taking in developing ToM and emotion understanding prompted us to design a visuospatial-based ToM training. The study aims to determine whether training young children’s visuospatial perspective-taking promotes their theory of mind and emotion understanding.

This study involves two training studies to investigate the causal relationship between visuospatial perspective-taking and mental state understanding. In study 1, children aged 4.5 years will be randomly assigned to participate in either (a) altercentric block building (experimental group) or (b) egocentric block building (control group). Experimenters will train children’s visuospatial perspective-taking through a series of block-building activities. Several studies have shown that block building fosters young children’s spatial development [83–85]. The training structure is to reproduce block figures because this task provides abundant age-appropriate experiences for children to grasp the visuospatial relations between objects. It should be noted that this study will specifically train young children to become visuospatial perspective-takers by requiring them to adopt the visual frame of their play partner (i.e., *altercentric block building*). In contrast, children in the control group will be required to reproduce the model figure that looks the same from their own viewpoint (i.e., *egocentric block building*). The partner’s perspectives are irrelevant; subsequently, children’s visuospatial perspective-taking will not be trained. Two research questions will be addressed in study 1: Is children’s visuospatial perspective-taking associated with their ToM and emotion understanding?Do children trained in the visuospatial perspective-taking group improve significantly more than the control children in ToM and emotion understanding after 6 weeks of training?

Previous studies have found that participating in block-building tasks enhances children’s general spatial and mathematics abilities [83, 84, 86, 87]. These two skills will be assessed as a manipulation check to ensure the training improves children’s relevant skills. In this way, any absence of effects will unlikely be attributable to manipulation failure.

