The main goal of study 2 is to determine whether visuospatial perspective-taking or conventional verbal training is more effective in enhancing children’s mind and emotion understandings. ToM training has mostly been heavily language-based because the literature has identified language as a strong correlate of ToM development [42, 44]. Visible social interaction without language input does not promote false-belief understanding. Hence verbal interaction is regarded to be crucial to mind understanding [88]. Moreover, a study by Lohmann and Tomasello [44] involving 3-year-old children also found that training on the theory of mind with minimal linguistic interaction was ineffective in improving children’s false belief understanding. On the basis of the embodiment framework, study 2 will investigate whether simulating the visuospatial experiences of others alone, i.e. *without* the presence of verbal communication, is sufficient to enhance mind and emotion understanding. By doing this, study 2 will compare the training effect caused by visuospatial perspective-taking to the one caused by mere verbal interaction. In study 2, children aged 4.5 years will be randomly assigned to participate in either (a) *socialised altercentric block building* (both visuospatial perspective-taking and verbal interaction), (b) *parallel altercentric block building* (visuospatial perspective-taking only), or (c) *paired dialogic reading* (verbal interaction only). Dialogic reading will be served as a promising interactive approach because this training involves back-and-forth verbal exchanges between children. In addition, dialogic reading is easy to administer with preschool children. The differences between groups in ToM and emotion understanding post-training would indicate whether visuospatial perspective-taking or verbal interaction group will be more effective in fostering mental state understandings. Two research questions will be addressed in study 2:

(1) What is the difference between the effect of visuospatial perspective-taking vs. general verbal interaction training on improving preschoolers’ ToM and emotion understanding?

(2) Do children trained in the socialised altercentric block building group improve significantly more than children in the parallel altercentric block building and paired dialogic reading groups in ToM and emotion understanding after 6 weeks of training?

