#### Design and procedures

This research proposal has gained approval from the Human Research Ethics Committee of [blinded university]. Written informed consent will be obtained from all participants' parents or legal guardians before the initiation of the study. Parents or legal guardians will be asked to complete a set of questionnaires on family demographics, children's characteristics and executive functioning. Prior to the training, children will first complete a pre-test in a quiet room at the University. Then, children will be randomly assigned to either the (a) egocentric block building or (b) altercentric block building training group. The training period will be six weeks, with a 1.5-h training session per week. The training will be conducted in a child-friendly lab at the University. After the training sessions are completed, the children will be tested with the same battery of measures in the post-test. Upon completion of the training, the participants' parents or legal guardians will receive a report of their child's performance and a gift voucher valued at HKD$200.

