#### Training activities

The children will be randomly grouped into pairs, and a trained experimenter will guide them. Like study 1, the experimenters will receive a three-hour training on the protocol, and their instructions and guidance will be regularly monitored. Children will be randomly assigned to one of three training groups, namely (a) *socialised altercentric block building*, (b) *parallel altercentric block building*, and (c) *paired dialogic reading*. Among the training groups, the socialised and parallel altercentric block building groups are based on the altercentric block building group in study 1. Both groups will also have the same gradation of difficulties in terms of model complexity and seating position as in study 1. The paired dialogic reading is derived from the conventional language-based training. The three different training activities are described below:

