**Table Tabb:** 

Training groups	Training activities	Visuospatial perspective-taking	Verbal Interaction
(a) *Socialised altercentric block building* (Fig. 3)	Two children will be seated next to each other, and a toy bear will be seated at 180°, 90°, or 270° angular difference to the line of sight of the children. The experimenter will present a model figure built from blocks. Children will be asked first to reproduce the figure based on their own visual frame. Then, they will be asked to adopt the visual frame of the toy bear and reproduce the figure. Note that the children will be encouraged to discuss the perspective of the toy bear when building the block-figure. Therefore, both visuospatial perspective-taking and verbal interaction will be trained in this group	✓	✓
(b) *Parallel altercentric block building* (Fig. 3)	This training group will have the same procedures as that in the (a) socialised altercentric block building group, except children in this group are required to reproduce the block-figure without discussing the perspective of the figurine. Therefore, only visuospatial perspective-taking will be trained in this group	✓	✗
(c) *Paired dialogic reading*	The storytelling intervention by Ornaghi et al. [101] will be adapted in this training group. The experimenter will read the book series "The Adventures of Jack and Theo" [102] to the children. Children will listen to three stories in each session. After each story, children will be engaged in different language games and conversations. This training will minimize the use of the mental state lexicon to avoid perspective-taking and mentalising. No block-building activity will be involved in the training group. Therefore, only verbal interaction will be trained in this group	✗	✓

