#### Data analysis plan

The preliminary analyses will be the same as those in study 1. Next, repeated measures MANOVAs will be conducted to compare the effectiveness of the three trainings in improving children’s visuospatial perspective-taking, ToM, and emotion understanding abilities. We predict all of the training in study 2 will increase children’s ToM and emotion understanding. In particular, we hypothesise that the *socialised altercentric block building* training will result in the greatest improvement on the children’s ToM and emotion understanding. We expect the paired dialogic reading to enhance children’s general language ability but not their visuospatial perspective-taking ability. In contrast, we expect that the *parallel altercentric block building* will enhance the children’s visuospatial perspective-taking ability but not their general language ability. We further hypothesise that the *socialised altercentric block-building* training will enhance both visuospatial perspective-taking and language abilities because verbal interaction may strengthen children’s developing ability to simulate the visuospatial experience of others. This finding will reveal whether visuospatial perspective-taking is conducive to developing ToM beyond the contribution of verbal interaction.

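### Three stated claims (Study 2 reproduces Study 1, perspective-taking alone suffices or all trainings work, spatial/maths gains exclude manipulation failure) go beyond the otherwise sound between-arm comparisons

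*Protocol article*

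**What the plan says.** **Study 1** randomises children to altercentric or egocentric block building. Both arms build blocks; they differ in whether the partner's view differs from the child's own (Training activities). The main repeated measures MANOVA compares change in ToM and emotion understanding between the arms. The Data analysis plan also asks whether perspective-taking improves more in the altercentric than in the egocentric arm.

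Separately, spatial and mathematics gains are examined in both groups. The present study section calls these two skills a manipulation check and concludes: "In this way, any absence of effects will unlikely be attributable to manipulation failure".

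**Study 2** has three arms: socialised altercentric building, parallel altercentric building and paired dialogic reading. The Background gives its purpose: "Study 2 aims to reproduce the results of Study 1, and more importantly, to elucidate and compare the engagement" of visuospatial perspective-taking and verbal interaction. The present study section says it will investigate whether simulating others' visuospatial experience, without verbal communication, "is sufficient to enhance mind and emotion understanding". The Data analysis plan adds: "We predict all of the training in study 2 will increase children’s ToM and emotion understanding".

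**Timing.** Training lasts six weeks, and "the children will be tested with the same battery of measures in the post-test". Study 2 repeats this procedure. The Participants section for Study 1 justifies the enrolled age by the fact that ToM and emotion understanding typically emerge at about 4 to 5 years.

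**The concern.** Each of the three claims needs a comparison that its study does not contain or does not use for that purpose.

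- *Reproducing* Study 1 needs Study 1's contrast, hence an egocentric arm.
- *Sufficiency*, and a rise caused by *every* training, need a reference for what six weeks and a second testing would do anyway.
- *Excluding manipulation failure* needs evidence that the ingredient separating the two Study 1 arms was delivered.

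Without these, children who simply grew older and met the same tests twice could supply apparent support for the claims. The Discussion raises the stakes. It intends to argue, if training improves these abilities, that individual variation is not entirely maturational, and gains without a reference cannot carry that argument.

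**Working it through.** **1. What the plan's sample sizes power.** Inputs from the two Participants sections: f = 0.32, alpha 0.05, power 0.80, MANOVA within-between interaction. With two time points and k groups, the test is a noncentral F with df1 = k − 1, df2 = N − k and λ = N·f².

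| Study | k | N | λ | Power |
|---|---|---|---|---|
| 1 | 2 | 79 | 79 × 0.1024 = 8.09 | 0.802 |
| 2 | 3 | 98 | 98 × 0.1024 = 10.04 | 0.804 |

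One child fewer gives 0.797 and 0.799, so the stated 79 and 98 are reproduced exactly. Both studies are sized for a difference in change *between* arms. Neither is sized for an absolute gain.

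**2. Can Study 1's contrast be formed in Study 2?**

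| | Study 1 | Study 2 block arms | Study 2 reading arm |
|---|---|---|---|
| Blocks | both arms | yes | no |
| Other viewpoint | partner: opposite (altercentric) or alongside (egocentric) | toy bear at 90°, 180° or 270°, children side by side | none |
| Peer discussion as the trained element | not a difference between arms | socialised yes, parallel no | yes |

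No Study 2 arm builds blocks without perspective-taking, so altercentric minus egocentric does not exist there. The nearest substitute, parallel building versus reading, differs in perspective-taking, verbal interaction and block building at once. The parallel arm also contains own-view building ("Children will be asked first to reproduce the figure based on their own visual frame"), as Study 1's control did. If parallel building beat reading, that would show an advantage over an active comparator, but it would not isolate perspective-taking.

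**3. What supports an absolute gain in Study 2?** A between-arm contrast can show that one arm gained more than another. It cannot show that all three gained because of training. Equal gains in all arms fit both *every training works* and *none works*.

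**4. What does Study 1's spatial/maths check show?** Both arms build blocks, mature and are retested. Gains in both could occur with no training effect. Even genuine gains would come from what the arms share, not from what separates them.

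**5. Illustration of size.** The documents give no figure for gain without training, so d, the gain in SD of the change score, is an assumption. For a two-sided 5% test on change, the noncentrality is d√n. Completers after the plan's 20% attrition: 40 × 0.8 = 32 per Study 2 arm; 96 × 0.8 = 76.8, taken as 76, in Study 1. With zero training effect:

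| d (assumed) | One Study 2 arm, n = 32: d√n | P(significant) | Study 1 pooled time effect, n = 76: d√n | P(significant) |
|---|---|---|---|---|
| 0.2 | 1.13 | 0.20 | 1.74 | 0.41 |
| 0.3 | 1.70 | 0.38 | 2.62 | 0.73 |
| 0.5 | 2.83 | 0.78 | 4.36 | 0.99 |

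At d = 0.1 the probabilities are about 0.09 and 0.14. With all 40 children retained in a Study 2 arm, d = 0.3 and 0.5 give 0.46 and 0.87.

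**The case against.** The strongest reply is that the plan's inference is already between-arm. Study 2's two research questions ask for differences between trainings, its MANOVAs compare the three, and its sample size is for the interaction. No within-arm test is specified. This stands. A reader might infer that Study 2 as a whole is undermined by maturation and retesting, or that it must have an untrained arm. The documents do not support that: randomisation protects its contrasts, and active comparators are a legitimate choice.

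Second, the sentence after the sufficiency wording ties it to a comparison with verbal interaction. This also stands, and it means the protocol does not rest sufficiency openly on pre-post change. But being better than reading is a relative finding, and *sufficient to enhance* is an absolute one. The contrast also carries block building with it.

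Third, *reproduce* may mean a conceptual replication, and the sentence ranks it below the comparison. That is a fair reading, but the text does not say so, and the only available contrast is the confounded one in step 2.

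Fourth, a reader might infer that Study 1's manipulation check as a whole would look the same if training did nothing. That is wrong. The planned between-arm comparison on the Perspective-Taking Test for Children (PTT-C) addresses delivery of the trained skill directly. The weakness is confined to the spatial/maths check and the sentence built on it.

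Finally, the percentages describe tests that the plan does not name, under assumed gains. That is true; they show scale only.

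**Conclusion.** The point holds as a limit on three stated claims. Study 2 cannot reproduce Study 1's contrast. Neither sufficiency nor a training-caused rise in all three arms can be established without a reference for untrained change. Spatial and maths gains in both Study 1 arms do not exclude manipulation failure. These conclusions follow from the described arms and need no numerical assumption.

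The illustrative false-support rates, 20% to 78% for one Study 2 arm and 41% to 99% for Study 1's pooled time effect, do depend on the assumed gain of 0.2 to 0.5 SD of change and on 20% attrition in both studies. At 0.1 SD they are far smaller.

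Study 1's main MANOVA, its PTT-C check and Study 2's group-by-time contrasts are unaffected for comparing arms. This should be fixed, because it changes what the trial may conclude, but it is a correction of claims and not a failure of the design.

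**What to change.** - **Background:** delete the aim of reproducing Study 1, or reword it as extending Study 1 with a modified task and different comparators.
- **The present study:** replace the sufficiency wording with a question about parallel building relative to reading, and note that these arms also differ in block building.
- **Study 2 Data analysis plan:** state that conclusions rest on group-by-time contrasts. Label within-arm gains, including the prediction that all trainings raise the outcomes, as descriptive.
- **Study 1 manipulation check:** rest the inference about manipulation failure on the between-arm PTT-C comparison already planned. Keep spatial and maths gains descriptive.
- **Study 2 manipulation check:** test spatial and maths gains as the two block arms against reading, a randomised contrast that the design already provides.

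The cost is rewording and one specified contrast, with no added participants. The downside is narrower claims for Study 2.

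If the sponsor prefers to keep the absolute claims, a fourth, reference arm would be needed; an untrained one serves the absolute claims, an egocentric one the replication aim. With k = 4 and the plan's own f, alpha and power, the interaction test needs N = 111 (power 0.802). Allowing for attrition, 111 / 0.8 = 138.75, so about 140 at 35 per arm, against 120 now.

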### Theory of mind and emotion understanding

Early studies on ToM development have been based on an either-or assumption. Such studies use false belief tasks to illustrate that a fully developed ToM is attained at around four years of age [9, 10]. More recently, researchers have considered the development of ToM to be a spectrum of mind understandings that occur over the course of development; ToM abilities unfold by successive insights that range from understanding of simple desires to more complex mental stances and perspectives [13–16]. On the basis of the spectrum of mental state understandings, individual differences in ToM among children become apparent [12, 17]. Even adults can make egocentric errors; past research has shown that adults may fail to resist interference from their own perspective when understanding the mental states and interpreting the behaviors of others [18, 19]. In the context of a communication game, bilingual adults’ ability to assume others’ mental states is also modulated by the cultural frame currently active in their mind [20]. These findings have sparked research into what makes individuals different when it comes to understanding the minds and emotions of others.

Emotion understanding involves appropriately comprehending and responding to emotional cues in social interactions [4]. Existing evidence shows that ToM and emotion understanding are related to one another, and are conceptually interrelated [2, 3, 21–23]. Longitudinal studies have revealed the relationship between ToM and emotion understanding, as well as the direction of influence between these two domains of social cognition: O’Brien and colleagues [24] investigated the relationship between ToM and emotion understanding and found that early emotion understanding at 3 years of age predicted later ToM performance at 4 years of age. Similarly, a recent longitudinal study by Kuhnert et al. [3] found significant associations between emotion understanding at 5 years and ToM at 7 years. These studies suggest that children’s emotion understanding precedes and supports their development of ToM.

Although emotion understanding occurs before ToM, ToM also contributes to children’s emotion understanding in social occasions. According to Eggum et al. [25], ToM appears to facilitate the understanding of the emotions of others, especially when the child’s emotional experiences differ from those of others. For example, ToM may assist a child who enjoys swimming in understanding that other children may be afraid of the water and experience fear in a pool. Children often draw on their ToM insights to assess other’s emotional responses.

